**Not applicable**

**Assessment Procedures.** Participants in both the incentives and best practices conditions will complete a formal assessment at intake, during early pregnancy (i.e., one month after enrolling), late pregnancy (i.e., 28-weeks gestation), and at 4-, 8-, 12-, and 24-weeks postpartum. This schedule of formal assessments and the use of similar questionnaires (see Assessment Battery) will permit comparisons to prior controlled trials conducted by our group. Participants will receive \$50 per formal assessment completed. This money may come in the form of a check mailed to their home or in the form of a gift card (TangoCard) that is emailed to them. TangoCard is an electronic gift card platform. If participants receive their rewards via this option, the reward will be emailed to them as a unique URL. By following the URL, the participant can choose from a variety of gift card brands and redeem their reward. Once they select a brand, the final gift card will be emailed to them. To ensure that HIPAA security standards are met and emails are kept private, TangoCard has signed a BAA (Business Associate Agreement) with DynamiCare. Questionnaires will be completed remotely via computer or mobile phone. Items will be administered using REDCap or SurveyGizmo, both of which capture and house unique de-identified codes for study participants. Data audits will be conducted monthly during the first six months of the study and then quarterly until study completion to detect problems. As no personal identifying information will be collected, the chance of a breach of confidentiality is very low. Regardless of whether participants complete the assessment online or over the phone, participants in both treatment conditions will be required to submit both a breath CO sample and a salivary cotinine sample at each formal assessment to determine their smoking status.

**Assessment Battery** Participant's intake assessment will be conducted after they have had their first prenatal visit and phone screen to determine preliminary eligibility and will address six areas: (a) Sociodemographics (age, educational attainment, race/ethnicity, marital status, health insurance status); (b) Medical/pregnancy history (height/weight, self-reported pre-pregnancy weight, weeks pregnant, history of complications in prior pregnancies; (c) Smoking history (age started smoking, pre-pregnancy time to first cigarette/cigarettes per day, past week time to first cigarette/cigarettes per day, number of quit attempts before/during the current pregnancy, number of other smokers in the household, rules about smoking in the household, nicotine dependence); (d) Smoking timeline follow-back (to characterize daily smoking rates and/or use of alternative tobacco products or nicotine replacement therapy since learning of the current pregnancy); (e) Smoking attitudes (motivation to stop, confidence in ability to stop, intention to quit before the baby is born, intention to remain abstinent after the baby is born, perceived stress levels); (e) Maternal health/executive functioning (lifetime history of depression, general psychiatric symptoms, current depressive symptoms, discounting of delayed hypothetical monetary rewards, behavioral economic measure of the reinforcing value of cigarettes, Behavior Rating Inventory of Executive Function®-Adult Form [BRIEF-A; see attached], EQ-5D Health-Related Quality of Life Questionnaire [see attached]); (f) Stressful life events (SAMHSA Life Events Checklist [see attached]). Appropriately modified versions of these measures will be administered at the other six formal assessments identified above. In addition, at the postpartum assessments we will assess breastfeeding, including initiation, duration, and different levels of breastfeeding (e.g., exclusive, predominant, any).

Participants randomized to the Incentives condition will have one additional measure administered at five of the six formal assessments that follow the intake assessment (early pregnancy, late pregnancy, 4-, 8-, and 12-weeks postpartum). This measure is an Episodic Future Thinking task (EFT; see attached) that requires them to imagine positive events that may realistically occur at various time points in the future. Participants will answer open-ended questions asking them to describe the event, who will be present, how they will feel, etc. They will also rate the event on a series of characteristics such as how positive, vivid, and detailed the future event is. The time points at which participants are asked to imagine future events will correspond to subsequent assessments (e.g., participants completing their early pregnancy assessment will be asked to imagine an event that may realistically occur by the time they reach their late pregnancy assessment). Instructions provided before and after the text explain the reason and potential benefits of engaging in EFT, and encourage participants to think about the cues that they generate in between assessments (e.g., first thing in the morning to set their day, when they experience cravings or feel tempted to smoke).

After each assessment is complete, research assistants will review participants' responses to the EFT questions, and may provide feedback about how participants can use their future event in their daily lives as motivation to quit smoking or to stay smoke-free. Participants may also receive notifications from the study app prompting them to think about their future events in between their formal assessments. The rationale for adding this component to the Incentives group only is that engaging in EFT may help these women sustain abstinence more effectively after the incentives are withdrawn at 12 weeks postpartum. Instructions and prompts to think about their future events and incorporate these cues into their daily lives further encourages participants to practice propection, and thus may be helpful in better sustaining long-term abstinence. Any texts that participants receive asking them to think about their future events will be automatically generated from the DynamiCare Rewards App. Since these messages will be auto-generated from the study app, they will not address the participants by name, and the content will not be specific to individual participants in the study, nor will the content include any personalized messaging or identifying information.

After participants' consent to join the study, we will collect contact information over the phone including their mailing address (to send them equipment), as well as the phone number for an alternative contact in the case that we are unable to reach the participant. We will also ask the participant to tell us how we should describe their involvement in the research study should we need to reach out to their alternative contact at some point. This form is attached, and it will be updated following each formal assessment. Keeping an updated mailing address is important in case participants need additional equipment or paperwork mailed to them.

We also plan to examine birth outcomes and their associated costs in order to gather basic data for a preliminary cost-effectiveness analysis. More specifically, project staff will obtain faxed copies of the delivery reports for all women enrolled in the study. Mom's verbal permission allowing researchers to recruit and collect medical record data about their infant will be documented during the informed consent process. For infants born at UVMHC, this will constitute permission to access infant health outcomes in PRISM. For infants born elsewhere, Mom's may be mailed a Medical Release Form (attached) after delivering their baby that they will sign and return in a stamped envelope pre-addressed to the UVM SATC ([name]), or they may view this medical release form and provide an electronic signature on RedCAP if the location where they deliver accepts e-signatures as a valid form of authorization. Regardless of whether signatures on the medical release form are obtained electronically or via the mail, this form will then be faxed to the clinics where they delivered. We use comparable methods to obtain infant medical record data in our current trial (CHRMS 13-143) and have received a vast majority of delivery reports for infants born outside UVMHC. Outcomes abstracted from the delivery report will include mean birth weight, % low birth weight deliveries (< 2500 g), mean gestational age at delivery, % premature deliveries (< 37 weeks), incidence of NICU admissions, and mean length of stay per NICU admission. Over the past 10 years, over 99% of women in our trials have provided permission to review maternal and infant medical records, so we anticipate no difficulty obtaining consent to collect these data in the proposed study. Our staff has substantial experience establishing relationships with local primary care clinicians, which facilitates the logistics of our staff coordinating with new clinics to review records.

Regarding the cost-effectiveness analysis, we will employ the Brief Drug Abuse Treatment Cost Analysis Program (Brief DATCAP;) to estimate the cost of delivering the Incentives versus Best Practices smoking cessation treatments. More specifically, we will derive the direct and indirect economic cost of treatment by allocating fixed costs based upon the proportion of time spent delivering these programs, as well as costs that vary by patient engagement and smoking status (e.g., staff time validating breath CO samples, quit-line staff time, incentives). Administration costs (e.g., postage/courier service to mail participants CO monitors) will also be included. Costs will be in USD for price year 2017/2018. The time period of the cost analysis will span from intake to discontinuation or completion of the program. However, since the duration of treatment will vary according to where in the pregnancy a woman enters the study, the economic cost per person per week will also be calculated. Research-specific resources consumed over the course of the study will be excluded from the cost-effectiveness analysis. Estimated treatment delivery costs will be combined with the delivery report outcomes above to conduct the preliminary economic evaluation (See Statistical Methods).

**Examining Acceptability.** At the 24-week postpartum assessment or shortly thereafter, participants in both

the incentives and usual care conditions will complete a Treatment Acceptability Questionnaire (TAQ) comparable to those administered in other financial incentives interventions, including research conducted by [name]. The measure will be administered on REDCap and will query participants about the ease of use, helpfulness, and convenience of the intervention, as well as whether the intervention was fair, fun, and whether they would recommend it. All responses will be made using a 100-point visual analogue scale. Participants in the incentives condition will receive additional TAQ questions inquiring about whether they liked self-monitoring their breath CO levels, engaging in EFT, earning vouchers, and whether the EFT tasks and the vouchers were helpful in terms of promoting smoking abstinence during treatment and sustaining abstinence following treatment withdrawal. In addition, research staff will call all participants upon completing the 24-week assessment/TAQ to query them about barriers and facilitators of treatment engagement including: (a) features of the intervention that they felt facilitated or hindered engagement (e.g., technical difficulties/availability of technical support, self-monitoring using the CO monitor, appropriateness of staff counseling surrounding smoking), (b) social/environmental variables (e.g., quit support from friends/family, rules about smoking in the home, exposure to smoke-free environments, social networks that promoted or discouraged quitting smoking) and (c) internal/psychological variables (e.g., stress, psychological well-being, motivation to quit, self-efficacy for quitting smoking). The semi-structured interview used to examine barriers and facilitators of treatment engagement will use scripted prompts, however participants will be able to respond freely and openly to each question. Their responses will be transcribed verbatim by the research staff completing the interviews.

**Statistical Considerations:** *Delineate the precise outcomes to be measured and analyzed. Describe how these results will be measured and statistically analyzed. Delineate methods used to estimate the required number of subjects. Describe power calculations if the study involves comparisons. Perform this analysis on each of the primary and secondary objectives, if possible.*

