biochemical verification of smoking status, which limits access to those in the immediate vicinity of clinics that can provide such care. ***Capitalizing on technological advancements may surmount such access barriers, with the potential to extend the reach of financial incentives to disadvantaged pregnant smokers nationwide.***

**The overarching aim of the current study is to develop an innovative, efficacious, remotely delivered financial incentives intervention to reduce cigarette smoking during pregnancy.** To enable flexible use of the intervention in diverse locations, we will use a mobile-phone-based platform for delivering the incentives intervention. Recent data indicate that over 80% of pregnant women drawn from a U.S. nationally representative sample own a smartphone. The platform will involve a Smartphone “app” which uses video capture to verify smoking status via a breath carbon monoxide (CO) monitor along with saliva cotinine test kits, and ensures treatment fidelity by providing automated, immediate feedback, incentive calculations, and incentive delivery for abstinence. Comparable technology-based treatment delivery platforms have been used to successfully promote smoking abstinence among the general population of U.S. smokers and among other vulnerable populations including rural heavy smokers.

The proposed study addresses the following specific aims:

**Aim 1:** Examine the feasibility, efficacy, and cost-effectiveness of a mobile-phone-based incentives intervention for promoting smoking cessation among economically disadvantaged (i.e., Medicaid insured) pregnant women. We will accomplish this aim by randomly assigning 152 pregnant women who are still smoking at their first prenatal care visit to receive incentives contingent on biochemically verified smoking abstinence or best practices for promoting smoking cessation. Incentives will be in place from the start of prenatal care through three months postpartum. Primary outcomes will be point prevalence smoking abstinence, continuous abstinence during and following pregnancy, and birth outcomes (mean birth weight, gestational age, NICU admissions). We hypothesize that there will be higher abstinence rates, longer durations of abstinence, and improved birth outcomes in the incentives versus the best practices condition.

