#### **Statistical Methods**

Study conditions will be compared on baseline demographics and other characteristics using analysis of variance (ANOVA) for continuous variables and chi-square tests for categorical variables. If a specific characteristic differs significantly across study conditions and is predictive of the outcome, it will be considered as a potential covariate in subsequent analyses. Analyses of treatment effects on smoking status will adhere to an intent-to-treat approach whereby all women randomized to each study condition will be included in the analyses independent of early dropout, noncompliance, etc., with the exception of women excluded for abortion/fetal demise as is convention in this research area. Cochran-Mantel-Haenszel tests (C-M-H) will be performed for comparisons between the incentives vs. usual care conditions on point-prevalence smoking abstinence at end-of-pregnancy and 6-months postpartum assessments with referring clinic as a stratification variable. The Breslow-Day Test will be used to examine the homogeneity of treatment effects across referring clinics. Comparisons of point-prevalence abstinence rates between treatment conditions across all assessments through six months postpartum will be analyzed using mixed model repeated measures for categorical data based on generalized estimating equations (GEE) using a logistic link function (SAS: PROC GENMOD, SAS Institute, Cary, NC). The two treatment groups will also be compared on birth outcomes, breastfeeding, and other measures collected postpartum. Comparisons of treatment conditions on dichotomous outcomes (e.g., % low birth weight, % preterm, % NICU admissions, % breastfeeding) will parallel categorical analyses for point prevalence abstinence using PROC GENMOD to adjust for strata (referring clinics) and potential covariate effects. Analysis of covariance (ANCOVA) will be used to compare study conditions on mean birth weight adjusting for variables known to influence birth weight (% maternal pre-pregnancy BMI, parity, and sex) and mean gestational age at delivery. The significance criterion will be set at  $\alpha = 0.05$  for all analyses.

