Regarding the cost-effectiveness analysis (CEA), the CEA will be conducted by dividing the average (mean) difference in treatment costs across the incentives versus best practices conditions by the average (mean) difference in each outcome (abstinence rates in late pregnancy, birth outcomes) to derive incremental cost-effectiveness ratios (ICERs). Statistical significance of these ICERs will be determined probabilistically by employing non-parametric bootstrapped standard errors. The main objectives of this preliminary CEA will be to (a) establish methods for obtaining and analyzing data that pertain to both treatment delivery and birth outcomes in remote financial incentives interventions, and (b) comparing ratios on key birth outcome measures and NICU admissions. These basic CEA data will provide important preliminary data for a future RO1 application in which we may propose conducting a more sophisticated cost-effectiveness analysis that incorporates both birth outcomes and infant health outcomes assessed over a longer time period (e.g., medical illnesses throughout the infant's first year of life).

Regarding the acceptability data, TAQ items administered using a 100-point VAS will be compared across the two treatment conditions using ANOVA's. Again characteristics that differ across treatment condition will be considered as potential covariates. Responses to the semi-structured interview questions will be transcribed directly during the interview and analyzed afterwards using a thematic content analysis. We will employ an inductive approach whereby the content of these qualitative data will direct the coding and theme development. Coding of the data will involve grouping, sorting, and identifying themes that reflect barriers and facilitators of treatment engagement. Two researchers will perform the content analysis independently and sort responses into

themes. Disagreements will be resolved through discussion until consensus is reached. Those themes that emerge and reflect modifiable aspects of the intervention (e.g., provision of technical support, appropriateness of staff counseling and feedback surrounding quitting smoking) will be taken into account in designing future iterations of this intervention that are more responsive to participant's preferences.

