**Inclusion of Children:** Describe efforts to include children. Inclusion is required unless a clear and compelling rationale shows that inclusion is inappropriate with respect to the health of the subjects or that inclusion is inappropriate for the purpose of the study. If children are included, the description of the plan should include a rationale for selecting or excluding a specific age range of children. When included, the plan must also describe the expertise of the investigative team in working with children, the appropriateness of the available facilities to accommodate children, and the inclusion of a sufficient number of children to contribute to a meaningful analysis relative to the purpose of the study. **If children are excluded then provide appropriate justification. Provide target accrual for this population.**

As we plan to collect limited health information about the infants born to Mom's enrolled in the study, Mom's will provide permission to recruit and collect the following pieces of information about their infants: birth weight, gestational age at delivery, whether the infant was admitted to the NICU, and duration of NICU stay. Collecting these data are necessary in order to evaluate effects of this novel treatment on infant birth outcomes and to complete the proposed basic cost-effectiveness analysis. Mom's will be informed during the consent process about the specific pieces of information that we plan to collect about their infant, and the reasons for collecting this information.

*For protocols including the use of an investigational drug, indicate whether women of childbearing potential have been included and, if not, include appropriate justification.*

N/A

*If HIV testing is included specifically for research purposes explain how the test results will be protected against unauthorized disclosure. Include if the subjects are to be informed of the test results. If yes, include the process and provision for counseling. If no, a rationale for not informing the subjects should be included.*

☒ **Not applicable**

**Recruitment:** Describe plans for identifying and recruitment of subjects. All recruitment materials (flyers, ads, letters, etc) need to be IRB approved prior to use.

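### NICU stay is defined per NICU admission, so comparing it between arms conditions on a post-randomisation outcome that incentives are expected to reduce; it could mislead if used in the arm comparison or the cost-effectiveness ratios.

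*Protocol*

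**What the plan says.** The birth-outcomes paragraph that follows Assessment Battery in the Protocol lists what will be abstracted from delivery reports. The list ends with "incidence of NICU admissions, and mean length of stay per NICU admission". The denominator for stay is thus written into the Protocol: admitted infants only. No section defines NICU days over all infants.

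Purpose and Objectives, Aim 1, counts "birth outcomes (mean birth weight, gestational age, NICU admissions" among the primary outcomes. It hypothesises "improved birth outcomes in the incentives versus the best practices condition". Length of stay is not on that list.

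Statistical Methods states: "The two treatment groups will also be compared on birth outcomes, breastfeeding, and other measures collected postpartum". It assigns a dichotomous analysis to "low birth weight, % preterm, % NICU admissions, % breastfeeding" and covariance analysis to mean birth weight. It names no method for length of stay.

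On the economic side, the cost paragraph before Examining Acceptability says: "Estimated treatment delivery costs will be combined with the delivery report outcomes above to conduct the preliminary economic evaluation". Statistical Methods forms each ICER by dividing the mean cost difference by the mean difference in each outcome, with birth outcomes among them. One stated aim there is "comparing ratios on key birth outcome measures and NICU admissions".

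Inclusion of Children lists the infant data to be collected, including "whether the infant was admitted to the NICU, and duration of NICU stay".

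**The concern.** Admission to the NICU happens after randomisation and is an outcome that the trial hopes to change. A mean taken only over admitted infants compares two groups selected by that outcome. If incentives alter which infants are admitted, the admitted infants in the two arms are no longer alike, and a difference in their mean stay mixes the treatment effect with the change in who is admitted.

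The result can go in any direction. If the admissions averted are disproportionately short, those that remain are longer on average, and the arm with fewer admissions and fewer total NICU days shows a longer stay per admission. If short and long admissions fall in the same proportion, the measure shows nothing although total days fall.

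What is at stake is the reading of a birth outcome and, if stay is used as an ICER denominator, the sign or size of that ratio. Statistical Methods says that establishing methods is a main aim of this preliminary evaluation and that its data are meant for a later grant application, so a poor definition could carry forward.

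**Working it through.** **Plan figures.** The Protocol gives no NICU admission rate, no length of stay and no power for either, so there is no NICU figure to reproduce. The only planning number used below is 76 women per condition (Sample Size Justification). That size does reproduce for abstinence: a two-sided chi-square test at 0.05 has 80.5% power for 20% vs 5% and 99.3% for 40% vs 10%. The present point does not depend on it.

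**Assumed inputs.** Let p_S and p_L be the control proportions of infants with a short or a long NICU stay, d_S and d_L the mean days of each, and r_S and r_L the factors by which incentives multiply p_S and p_L. All six are assumptions. Control admission is varied from 10% to 20%, short stays from 3 to 5 days and long stays from 14 to 30 days.

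**Formulas** (incentives arm; set r_S = r_L = 1 for control)
- Days per infant = p_S·r_S·d_S + p_L·r_L·d_L
- Admission rate = p_S·r_S + p_L·r_L
- Stay per admission = days per infant ÷ admission rate

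If neither factor exceeds 1 and at least one is below 1, days per infant must fall. Stay per admission rises if r_S < r_L, is unchanged if r_S = r_L, and falls if r_S > r_L. Its direction therefore depends on which admissions are averted, not on whether NICU use fell.

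**Base case.** With p_S = 0.10, p_L = 0.05, d_S = 4 and d_L = 20, control days per infant = 0.10×4 + 0.05×20 = 1.40. The admission rate is 0.15 and stay per admission is 1.40/0.15 = 9.33 days.

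| Effect of incentives | Admission rate | Stay per admission | Days per infant |
|---|---|---|---|
| Short halved, long unchanged | 0.100 | 1.20/0.100 = 12.00 (+2.67) | 1.20 (−0.20) |
| Short halved, long −20% | 0.090 | 1.00/0.090 = 11.11 (+1.78) | 1.00 (−0.40) |
| Short −30%, long −10% | 0.115 | 1.18/0.115 = 10.26 (+0.93) | 1.18 (−0.22) |
| Both −30% | 0.105 | 0.98/0.105 = 9.33 (0.00) | 0.98 (−0.42, i.e. −30%) |
| Short unchanged, long halved | 0.125 | 0.90/0.125 = 7.20 (−2.13) | 0.90 (−0.50) |

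**Other assumed bases**
- 15% short (3 days) and 5% long (14 days), with short halved and long −10%: stay per admission goes from 1.15/0.20 = 5.75 to 0.855/0.12 = 7.13 days, while days per infant fall from 1.15 to 0.855.
- 5% short (5 days) and 5% long (30 days), with short halved: stay per admission goes from 1.75/0.10 = 17.50 to 1.625/0.075 = 21.67 days, while days per infant fall from 1.75 to 1.625.

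**Consequence for an ICER that uses stay.** In the first table row the denominator would be +2.67 days per admission instead of −0.20 days per infant, so its sign is opposite. In the fourth row it would be 0.00 and the ratio undefined, although days per infant fell by 0.42.

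**Infants contributing.** Over these scenarios, 76 × admission rate gives 7.6 to 15.2 control infants and 5.7 to 9.5 incentives infants in the per-admission mean.

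**The case against.** The strongest reply is that the Protocol may never compare this quantity. The birth-outcomes paragraph is an abstraction list, Aim 1 omits stay, and Statistical Methods names no test for it. The sentence on NICU in the cost-effectiveness aims refers to admissions, not stay. The birth-outcomes paragraph mentions costs associated with birth outcomes, but nowhere are NICU days priced. Stay per admission may be meant as description only. This limits the point. A reader might infer that the plan prespecifies a test of stay, or that the economic evaluation will credit incentives with longer stays. The documents do not support either. Use of stay in an ICER follows only from the wording that carries the listed delivery-report outcomes forward, so the most that can be said is that it could mislead. But no section excludes stay from the comparison or the ratios, and the per-admission denominator is a stated definition, not a detail left open.

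A second reply is that admission incidence is listed and analysed beside stay, and that the product of the two gives days per infant (0.15×9.33 = 1.40; 0.10×12.00 = 1.20). A careful reader could make that correction for the point estimates. The ICERs as described, however, take each outcome in turn and not the product.

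A third reply is that the reversal depends on which admissions are averted, and the Protocol gives no reason to expect mainly short ones. That stands. A reader might take the reversal as expected, but the working shows that no change, or agreement of both measures, is equally open.

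Last, days per infant would still rest on a few long stays. That stands too. In the first table row, long stays supply 1.00 of 1.20 days (83%) in the incentives arm, from 0.05×76 = 3.8 expected infants.

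**Conclusion.** The point holds as one of definition. Stay per NICU admission is a mean over a group selected by a post-randomisation outcome that the trial expects to improve, so a between-arm difference in it is not a randomised comparison. Over the assumed inputs, the difference per admission ran from −2.13 to +4.17 days while days per infant fell in every case, and it was exactly zero in a case where days per infant fell 30%. These figures show what is possible. They do not predict the trial's result, because the Protocol supplies no NICU rates or stays.

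The consequence is modest. Stay is not among the primary outcomes named in Aim 1, no test is specified for it, and neither the abstinence conclusions nor the sample size depends on it. The change is still worth making, because the Protocol carries birth outcomes and delivery-report outcomes into the arm comparison and the economic evaluation without excluding stay.

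**What to change.** In the birth-outcomes paragraph, define the comparative outcome as NICU days per infant, counting 0 for an infant not admitted, over all infants with delivery data and by randomised arm. Use that quantity wherever NICU stay enters the arm comparison or the ICERs. Keep mean stay per admission as a descriptive figure beside the admission rate.

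The cost is about one line of text. Both inputs, admission status and duration, are already on the list in Inclusion of Children, so nothing new is collected. Some delivery reports may be missing, as with the outside births in the group's current trial, hence the restriction to infants with delivery data.

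There is a small downside: the new measure has many zeros, is skewed and still depends on a few long stays. The change removes the selection bias but not the imprecision. The non-parametric bootstrap already planned for the ICERs in Statistical Methods is suitable for its interval.
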